### Follow-up

Subjects in all four arms of the study will be followed up, three times in 12 months following recruitment. Blood pressure measurement for treatment outcome will be done. The Self-efficacy for Appropriate Medication Adherence Scale (SEAMS) is an adherence-monitoring scale that will be used to collect information from participants regarding their adherence to medication self-reporting. Apart from SEAMS, self-reporting pill counting for measuring medication adherence will be used, and health-related quality of life using EuroQol 5-Dimension-3-level (EQ-5D-3L) and a visual analog scale (EQ-VAS) will also be assessed. All the above assessments will be done at baseline, 6 months, and 12 months of follow-up.

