We will assess self-reported information regarding the number of tablets that will be utilized by participants within the specified timeline divided by the number of pills prescribed for that time multiplied by a hundred for the last 7 days. A rate of ≥ 80% will be considered adherent and vice versa [7, 8]; thereby, the percentage of participants who are successful in achieving adherent status between baseline and 12 months will be evaluated. In addition, to measure the adherence score at baseline, 6 months, and 12 months post-intervention, an Urdu/English version of the “Self-efficacy for Appropriate Medication Adherence Scale” (SEAMS) will be employed [33, 34]. The SEAMS is a 13-item measure for evaluating medication self-efficacy in chronic disease management that looks to be appropriate for people with low literacy abilities [34]. This survey will use a three-point response system, with 1 indicating lack of confidence, 2 indicating moderate confidence, and 3 indicating extreme confidence. The 13-item scale had a range of possible scores from 13 to 39. High scores indicate better adherence.

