### Statistical analysis

The intention-to-treat analytic method will be conducted [35, 36]. Mixed-effects modeling with repeated measures will be employed for the primary outcome change in systolic blood pressure at 0, 6, and 12 months. To estimate treatment effects at each time point, an interaction between time and the groups will be fitted. For the primary and secondary outcomes measuring systolic blood pressure and medication adherence difference between and with the group at 0, 6, and 12 months, parametric (ANOVA/repeated measure ANOVA) and non-parametric tests *(*Kruskal*-*Wallis test*/*Friedman test/Wilcoxon signed*-*rank test) will be used. We shall account for the multiple time points statistically by using Tukey’s exact test. The Tukey test will be utilized for multiple comparisons and adjustment for multiple comparisons will be performed by Bonferroni correction. All the outcomes will be analyzed at 0, 6, and 12 months; however, the final analysis will be at 12 months from baseline. The *p*-value for the significance test will be set at *p* < 0.05. Pill counting data, adherence assessment at dichotomous variables, frequencies, and the chi-square test will all be used. By using the general estimating equation (GEE) with negative binomial regression, at 12 months post-follow-up, the covariates affecting primary and secondary outcomes including, age, gender, ethnicity, living status, education, monthly income, use of reminder, health insurance coverage, body mass index (BMI), diabetes, duration of illness, number of comorbid conditions, number of daily medication use, dose frequency will be determined and controlled. A complete analysis plan will be established for data analysis, including subgroup analyses and sensitivity analyses.

Sub-group analyses of the change in systolic blood pressure, the adherence to medication over the previous 12 months will be conducted by age (21–29 years, 30–49 years, 50 years and above), sex (male, female), adherence (SEAMS, pill-counting), and health-related quality of life (using EQ-5D-3L and EQ-VAS). Missing data from attrition will be handled using a multiple imputations approach at 12 months.

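### The chi-square test named for yes/no pill-count adherence is valid between arms at 12 months, but leaves the baseline status already collected unused

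*Protocol article*

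**What the plan says.** Under Outcome measures, the self-reported pill count over the last 7 days is turned into a yes/no result: "A rate of ≥ 80% will be considered adherent and vice versa". The stated target is that "the percentage of participants who are successful in achieving adherent status between baseline and 12 months will be evaluated". The Follow-up section lists the pill count among the measures and adds: "All the above assessments will be done at baseline, 6 months, and 12 months of follow-up".

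The Statistical analysis section has three statements that could bear on this outcome.

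- For the dichotomous form it says: "Pill counting data, adherence assessment at dichotomous variables, frequencies, and the chi-square test will all be used".
- For the "medication adherence difference between and with the group at 0, 6, and 12 months" it names ANOVA or repeated-measures ANOVA, with Kruskal-Wallis, Friedman and Wilcoxon signed-rank as the non-parametric options. It does not say whether adherence there means the SEAMS score, the pill count or both.
- It plans a covariate analysis: "By using the general estimating equation (GEE) with negative binomial regression, at 12 months post-follow-up, the covariates affecting primary and secondary outcomes" are to be determined and controlled. The list that follows covers demographic, social and clinical variables. Adherence at baseline is not among them.

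On timing it says: "All the outcomes will be analyzed at 0, 6, and 12 months; however, the final analysis will be at 12 months from baseline".

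**The concern.** The outcome is binary, repeated on the same patients, and framed from baseline to 12 months. The one sentence written for the dichotomous form names a test with no place for a second measurement on the same patient. What this costs depends on how the test is used.

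- **Between arms at 12 months.** The test is valid. It gives up whatever precision baseline adherent status would bring, although that status is recorded for every patient.
- **Baseline against 12 months within one arm.** The two answers come from the same patient. With positive correlation, the unpaired standard error is too large, and a real change may be missed.

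The first use matters more, because it is the randomised comparison for one of the trial's stated objectives.

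**Working it through.** **The plan's own figure.** Sample size section: SD 18.5, means 148 and 143, two-sided 5%, 90% power, 30% attrition.

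n = 2 × (1.960 + 1.282)² × 18.5² / 5² = 287.7, so 288 per group. 288 / 0.7 = 411.4, so 412; 4 × 412 = 1648. This reproduces exactly. It concerns systolic blood pressure; no power is stated for the pill count.

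**Inputs for the binary outcome**

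- 288 completers per arm (from the calculation above).
- Baseline and control-arm adherence 62.3%, from the 37.7% non-adherence in the Background (100 − 37.7). Using it for this trial is an assumption.
- 72.3% in the intervention arm at 12 months: an assumed 10-point difference.
- Correlation ρ between a patient's baseline and 12-month status: not in the documents, taken as 0.2 to 0.7.
- One pairwise comparison at two-sided 5%, with no multiplicity correction.

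**Between arms at 12 months, chi-square**

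- Pooled rate 0.673; SE under the null = √(2 × 0.673 × 0.327 / 288) = 0.03909.
- SE under the alternative = √[(0.623 × 0.377 + 0.723 × 0.277) / 288] = 0.03887.
- Power = Φ[(0.10 − 1.96 × 0.03909) / 0.03887] = 73%.

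**The same contrast with baseline status used.** The variance is multiplied by about (1 − ρ²), so power ≈ Φ[0.10 / (0.03887 × √(1 − ρ²)) − 1.96]. Because that factor belongs to linear adjustment, I also simulated 40,000 trials per setting and tested with a Mantel-Haenszel test stratified by baseline status.

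| ρ | chi-square | approximation, baseline used | simulation, baseline used |
|---|---|---|---|
| 0.2 | 73% | 74.7% | 74% |
| 0.3 | 73% | 76.9% | 77% |
| 0.5 | 73% | 84.4% | 84% |
| 0.7 | 73% | 95.0% | 95% |

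In the simulation both tests held their false-positive rate at about 5%.

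**The contrast must be the 12-month one.** If the change from baseline is compared between arms, the variance factor is 2(1 − ρ) instead. At ρ = 0.3 it is 1.4, and power = Φ[0.10 / (0.03887 × √1.4) − 1.96] = 58%, below plain chi-square. At ρ = 0.5 the factor is 1 and nothing is gained.

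**Within one arm, 62.3% to 72.3%, if chi-square were used there.** With no true change, its false-positive rate is 2 × [1 − Φ(1.96 / √(1 − ρ))].

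For power at ρ = 0.5, the proportion adherent at both visits is 0.623 × 0.723 + 0.5 × √(0.623 × 0.377 × 0.723 × 0.277) = 0.559. The discordant proportion is (0.623 − 0.559) + (0.723 − 0.559) = 0.228.

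- McNemar: Φ[(0.10 × √288 − 1.96 × √0.228) / √(0.228 − 0.01)] = 95%.
- Unpaired chi-square: Φ[(0.10 − 1.96 × 0.03909) / √((0.228 − 0.01) / 288)] = 80%.

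| ρ | chi-square false-positive rate | chi-square power | McNemar power |
|---|---|---|---|
| 0.2 | 2.8% | 75% | 81% |
| 0.3 | 1.9% | 76% | 86% |
| 0.5 | 0.6% | 80% | 95% |

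**The case against.** The strongest reply is that the sentence on the dichotomous form gives no visit and no pairing. The final analysis is at 12 months, and there a four-arm chi-square has one answer per patient. The outcome may even be read as one result per patient, achieved or not achieved. This stands. A reader might infer that the plan treats repeated answers as independent and loses much of its power, but nothing in the document says the test will be applied across visits. Nor does it say that the three visits will be pooled between arms. Pooling would raise false positives: with variance factor 1 + 2ρ, the type I error is 9.8% at ρ = 0.2 and 16.6% at ρ = 0.5.

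A second reply is that chi-square is not the only method that could reach this outcome. The repeated-measures sentence covers medication adherence, and Friedman's test on 0/1 data is equivalent to Cochran's Q. The GEE covers secondary outcomes. This stands in part. Neither names the pill-count status, and Cochran's Q addresses change within a group, not arms. The GEE is given a count distribution and is set at 12 months. Its covariate list omits baseline adherence, although the list is introduced as inclusive and may not be complete.

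A third reply is that the article promises a complete analysis plan, so the choice of binary model can wait. That would answer a complaint about missing detail. Here a specific test is named, and a better use of the data is available.

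Lastly, the larger losses, those within an arm, concern a comparison that is not randomised. That is correct, and the conclusion does not rest on them.

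**Conclusion.** The point holds as an efficiency improvement to a secondary analysis. The named test is not invalid for the 12-month comparison of arms, but it leaves collected information unused. For 62.3% against 72.3% with 288 completers per arm, using baseline status adds about 1 to 4 points of power at correlations of 0.2 to 0.3, about 11 at 0.5 and about 22 at 0.7. The rates, the difference and the correlation are assumptions, so no single loss can be stated, and at low correlation the gain is small. The too-conservative behaviour arises only if chi-square is used for within-arm change, which the document neither plans nor rules out. The sample size and the primary analysis are not touched.

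**What to change.** In the Statistical analysis section or the analysis plan:

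1. Compare 12-month adherent status between arms with a logistic (binomial) model adjusted for baseline adherent status. Alternatively, fit a logistic mixed model or binomial GEE to the 6- and 12-month results, with arm, visit, arm-by-visit and baseline status as a covariate.
2. State that the estimate of interest is the between-arm contrast at 12 months, not the change-from-baseline interaction.
3. Report a standardised risk difference beside the odds ratio.
4. Keep chi-square for single-visit tables comparing arms.
5. For any within-arm change, use McNemar's test (two visits) or Cochran's Q (three visits), labelled descriptive.

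The cost is a few sentences and slightly more analysis work. No extra patients, visits or data items are needed. The one drawback, that odds ratios are harder to read, is met by item 3.

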**Methods:**

We chose a double-blinded pragmatic randomized-controlled with factorial design for this investigation. The trial is going to recruit 1648 hypertensive patients with coronary artery disease at the age of 21 to 70 years. All participants will already be on anti-hypertensive medication and own a smartphone. They will be randomized into four groups with each having 412 participants. The first group will only receive standard care; while the second group, in addition to standard care, will receive monthly Ed-counselling (educational booklets with animated infographics and peer counseling); the third group will receive daily written and voice reminders and an education-led video once weekly together with standard care; while the fourth one gets both interventions given to second and third groups respectively. All groups will be followed-up for 1 year (0, 6, and 12 months). The primary outcome will be the change in systolic blood pressure while secondary outcomes include health-related quality of life and changes in medication adherence. For measuring changes in systolic blood pressure (SBP) and adherence scores difference at 0, 6, and 12 months between and within the group, parametric (ANOVA/repeated measure ANOVA) and non-parametric tests *(*Kruskal*-*Wallis test*/*Friedman test*)* will be used. By using the general estimating equation (GEE) with negative binomial regression, at 12 months, the covariates affecting primary and secondary outcomes will be determined and controlled. The analysis will be intention-to-treat. All the outcomes will be analyzed at 0, 6, and 12 months; however, the final analysis will be at 12 months from baseline.

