### Outcome measures

The primary outcome measure is the change in participants’ systolic blood pressure at 0, 6, and 12 months. It will be recorded by a nurse who will be oblivious to the study participants’ group. MODEL-605P YAMASU, a calibrated upper-arm mercury sphygmomanometer, will be utilized for this purpose. The blood pressure of the participant will be measured according to standard procedures. Two different readings will be collected within 5 min; the average measurement will be the final measurement. If the difference between the two measures is greater than 5 mmHg, a third evaluation will be performed, with the average of the two closest measurements being used as the final measurement [30].

In accordance with this, we are going to measure the proportion of participants who will achieve systolic blood pressure ≤ 140 mmHg. There are several secondary outcomes to be investigated. Health-related quality of life baseline, 6 months, and 12 months after the intervention will be measured via the EuroQol 5-Dimension- 3-level (EQ-5D-3L) [31, 32]. The five dimensions include mobility, self-care, normal activities, pain or discomfort, and anxiety or depression. Each dimension has three levels: no difficulty, moderate problems, and serious problems. In addition, we are using the EQ-VAS to measure the patient’s self-rated health on a vertical visual analog scale, with two unique endpoints such as “Best imaginable health condition” for a score of 100 and “Worst imaginable health state” for a score of 0 [31].

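### The covariate-adjusted analysis is a negative binomial GEE, a count model that cannot be fitted to change in SBP and does not suit the other outcomes

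*Protocol article*

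**What the plan says.** The Statistical analysis section of the protocol article assigns one method to covariate adjustment: "By using the general estimating equation (GEE) with negative binomial regression, at 12 months post-follow-up, the covariates affecting primary and secondary outcomes". Fourteen covariates follow, from age and gender to dose frequency. The abstract repeats the method: "By using the general estimating equation (GEE) with negative binomial regression, at 12 months, the covariates affecting primary and secondary outcomes will be determined".

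The outcomes it is meant to serve are defined under Outcome measures:

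- Primary: "The primary outcome measure is the change in participants’ systolic blood pressure at 0, 6, and 12 months". Each SBP value is a mean of readings: "the average measurement will be the final measurement".
- Binary SBP control: "we are going to measure the proportion of participants who will achieve systolic blood pressure ≤ 140 mmHg".
- Pill-count adherence: tablets taken over tablets prescribed, as a percentage, dichotomised at 80%.
- SEAMS: a sum score from 13 to 39.
- EQ-VAS: a scale from 0 to 100. EQ-5D-3L: five dimensions with three ordered levels each.

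The Study design section also lists the number of tablets taken, which is a count. It is bounded by the number prescribed, and Outcome measures converts it to the percentage above.

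The Statistical analysis section names a different model for the primary comparison: "Mixed-effects modeling with repeated measures will be employed for the primary outcome change in systolic blood pressure at 0, 6, and 12 months", with a time-by-group interaction. No covariates are listed for that model.

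**The concern.** Negative binomial regression describes non-negative counts. It models the log of the mean and takes the variance as μ + kμ². None of the outcomes, as finally defined, is an unbounded count, and the primary one takes negative values. This is not a detail left open for a later analysis plan: the article names a distribution family, and the family does not fit.

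The adjusted analysis is the only one for which covariates are listed. If it cannot be run as written, someone will have to replace the family, the link and perhaps the form of the outcome (change or level) once data are in hand. That is avoidable analytic freedom. If it is run on SBP level instead, the result comes out as a ratio, whereas the research objectives ask for mean differences and the sample size is built on a difference in mmHg.

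**Working it through.** **Inputs.** From Sample size: SD of SBP 18.5 mmHg, means 148 and 143, two-sided 5%, power 90%, attrition 30%, 1648 in total (412 per group). From Outcome measures: the outcome types listed above. Assumed, because the article does not give them: the correlation between baseline and follow-up SBP (0.3 to 0.7), the mean change from baseline, the dispersion k, and the type of standard error.

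**1. The plan's own figure.** n per group = 2(1.96 + 1.2816)² × 18.5² / 5² = 287.7, so 288. Allowing for attrition, 288 / 0.70 = 411.4, so 412. Then 4 × 412 = 1648. This matches. It is a Gaussian comparison of two means in mmHg and uses no negative binomial quantity.

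**2. Change in SBP.** The log link needs a positive mean, and the distribution puts no probability on negative values. If SBP falls in an intervention group as hoped, the mean change there is negative. Fits to simulated changes (means −2 and −7, SD 18.5, 288 per group) failed: the GEE stopped on an undefined deviance and the likelihood fit returned undefined coefficients.

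Reversing the sign to a reduction does not help. A group with no mean change has mean 0, whose log does not exist. With SD of change = 18.5√(2(1 − ρ)), the share of participants with a fall is:

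| Mean change | ρ = 0.3 | ρ = 0.5 | ρ = 0.7 |
|---|---|---|---|
| 0 | 50% | 50% | 50% |
| −5 | 59% | 61% | 64% |

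So even at a mean change of −5, between 36% (100 − 64) and 41% (100 − 59) would be negative after the sign is reversed.

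**3. SBP level: scale.** The group coefficient is log(143/148) = −0.034, a ratio of 0.966. It is not a difference in mmHg.

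**4. SBP level: standard errors.** The observed variance is 18.5² = 342.

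- With k fixed at 1 and mean 148, the model variance is 148 + 148² = 22,052, an SD of 148.5. The standard errors are inflated by 148.5/18.5 = 8.0. At mean 143 the factor is 143.5/18.5 = 7.8.
- The dispersion that matches the data at mean 148 is (342.25 − 148)/148² = 0.0089.

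Simulation used 600 runs per setting, 288 per group and one record per person:

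| Dispersion | Standard error | Mean SE (no effect) | Rejection, no effect | Rejection, 5 mmHg |
|---|---|---|---|---|
| 1 | model-based | 0.0836 | 0% | 0% |
| 1 | robust | 0.0104 | 5.5% | 89% |
| 0.0089 | model-based | 0.0104 | 6.0% | 93% |
| 0.0089 | robust | 0.0104 | 6.3% | 92% |

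With no effect, the empirical SD of the estimate was 0.0106. The Monte Carlo error of a rejection rate near 90% is √(0.9 × 0.1/600), about 1.2 percentage points. Only the first row is badly wrong.

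**5. Other outcomes.** For a yes/no outcome the variance is p(1 − p), which is below p + kp² for every k ≥ 0, so the variance model is always too large. For SEAMS at mean 26 the largest possible variance is (26 − 13)(39 − 26) = 169; with k = 1 the model assumes 26 + 26² = 702.

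**The case against.** The strongest reply is that the primary result does not rest on this model. The mixed-effects model estimates group effects on SBP over time, and the GEE sentence is about which covariates matter and how they are controlled. That stands, and it limits the point to the adjusted analysis. The article does not say outright that the mixed model is unadjusted; it only lists covariates for the GEE and none for the mixed model.

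Several stronger readings are tempting and are not supported:

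- *SBP change will be negative for most participants.* The article gives no expected change from baseline and no SD of change; 148 and 143 are two population means. Under the assumptions above the share is 50% with no mean change and about 60% at −5. The argument needs no majority.
- *Standard errors will be eight times too large and power nil.* That requires dispersion fixed at 1 together with model-based errors. The article states neither.
- *None of the measurements is a count.* The number of tablets taken is one, though bounded and converted to a percentage.
- *A GEE at 12 months has one record per person, so it has no correlation to handle.* The phrase may give the timing of the analysis rather than restrict it to one visit, since the same section analyses all outcomes at 0, 6 and 12 months.

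It can also be said that a complete analysis plan is promised. It may correct the family, but the article states the wrong one in two places.

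**Conclusion.** The point holds for the covariate-adjusted analysis. For the primary outcome as defined, the stated model cannot be fitted. This follows from the outcome being signed and needs only that some participants have values below zero or that a group mean is not positive. For SBP level the model can be fitted, and with robust errors or a matched dispersion its inference is valid (rejection about 6% under no effect, 89% to 93% at 5 mmHg), but on a ratio scale that answers neither the stated objective nor the sizing assumption. The eightfold inflation is conditional on dispersion fixed at 1 with model-based errors. For the binary outcomes and bounded scores a count family is the wrong starting point.

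A reader might infer that the trial's main SBP comparison is lost. It is not: the mixed-effects model supplies it, and the sample size reproduces exactly without any negative binomial assumption.

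**What to change.** Delete the negative binomial family from the abstract and the Statistical analysis section, and name a family and link for each outcome:

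- SBP: Gaussian with identity link, either the mixed model already named with the listed covariates added or a GEE with robust errors. Report the effect in mmHg.
- SEAMS and EQ-VAS: Gaussian with identity link. This is a reasonable choice for bounded scores rather than the only defensible one.
- SBP ≤ 140 mmHg and adherence ≥ 80%: binomial with logit link, or modified Poisson.
- EQ-5D-3L: the article describes dimensions and levels only, so state what quantity is analysed and choose the family to match.

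Add one sentence on how the adjusted analysis relates to the primary mixed-effects model, and state whether the GEE uses all visits or the 12-month visit alone. The cost is a few sentences of text, best settled before the final analysis. No data collection changes, and the total of 1648 stays as it is.

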## Methods

### Study design

It is a factorial randomized controlled trial with a superiority design and a double-blinding approach. Intention-to-treat analysis with 12 months of follow-up will be applied to determine the efficacy of Ed-counselling assistance and mHealth intervention on hypertensive patients at four teaching hospitals in Lahore, Pakistan. Lahore is the provincial capital of Punjab (the largest province in the country) [21]. It is the world’s eighteenth-largest city and Pakistan’s second-largest metropolis. The SPIRIT 2013 Statement (Standard Protocol Items: Recommendations for Interventional Trials) [22] provides the basis for this research. A factorial approach will be used to assign participants to the four groups. The groups will receive standard care, Ed-counselling, mHealth intervention, and combined intervention (Fig. 1). All groups will be followed up for a period of total 12 months. Systolic blood pressure, the Self-efficacy for Appropriate Medication Adherence Scale (SEAMS), the number of prescribed tablets taken for a specified period (self-reporting), and health-related quality of life will be measured at least three times: at baseline, 6 months, and 12 months after the intervention [23, 24].

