### Sample size

For comparing different interventions among the four groups, the sample size is computed through the STATA software using a standard deviation of 18.5 in systolic blood pressure taken from a Pakistani study [9], population means of 148 and 143 respectively, as 5 mmHg reduction in systolic blood pressure is related to clinical importance regarding decreasing the risk of coronary artery disease [25]. A two-sided level of significance of 5% and a power of 90% with a 30% attrition rate between the baseline and 12 months of the intervention period were used. The total sample size calculated is 1648 with 412 in each group.

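### Repeated-measures ANOVA and Friedman stand beside the mixed model without ranking, and imputation is tied to 12 months, so participants without a month-6 value may drop out of analyses declared intention-to-treat, chiefly for adherence

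*Protocol article*

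**What the plan says.** The protocol commits to intention-to-treat twice: under Study design ("Intention-to-treat analysis with 12 months of follow-up will be applied") and under Statistical analysis ("The intention-to-treat analytic method will be conducted").

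Statistical analysis then sets out two families of method for the same visits:

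- a mixed-effects repeated-measures model with a time-by-group interaction, stated for SBP only;
- ANOVA or repeated-measures ANOVA, with Kruskal-Wallis, Friedman and Wilcoxon signed-rank as non-parametric counterparts, stated for both SBP and medication adherence. Dichotomised pill-count adherence goes to a chi-square test.

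No order of priority is given. The abstract lists the second family, "between and within the group, parametric (ANOVA/repeated measure ANOVA) and non-parametric tests", together with the GEE, and does not mention the mixed model.

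The only sentence on missing data is "Missing data from attrition will be handled using a multiple imputations approach at 12 months". All outcomes are to be analysed at 0, 6 and 12 months, with month 12 as the final analysis. The Sample size section plans for substantial loss: "A two-sided level of significance of 5% and a power of 90% with a 30% attrition rate between the baseline and 12 months".

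**The concern.** Classical repeated-measures ANOVA and Friedman need a value at every visit. A participant seen at baseline and month 12 but not at month 6 is removed from them, although the month-12 value was observed. If the imputation rule fills only month 12, nothing in the text restores that participant. Single-visit tests at month 6 would likewise rest on those who attended. An analysis restricted in this way is not intention-to-treat, and it can be biased if the reasons for missing month 6 differ between arms.

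The gap is foreseeable. Data management allows participants who cannot attend at 6 or 12 months to be interviewed by phone, whereas Outcome measures requires SBP to be taken by a nurse with a mercury sphygmomanometer. A phone contact can supply questionnaire answers but not that reading. Such a person has not left the trial, so a rule about attrition does not clearly reach them.

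Adherence is the more exposed outcome, because no mixed model is stated for it.

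**Working it through.** **1. The plan's own figure.** Inputs from Sample size: "using a standard deviation of 18.5 in systolic blood pressure"; "population means of 148 and 143 respectively", a difference of 5 mmHg; two-sided 5%; power 90%; 30% attrition.

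n per group = 2 × (1.960 + 1.282)² × 18.5² / 5² = 287.7, rounded up to 288. Inflated: 288 / 0.70 = 411.4, rounded up to 412. Total: 4 × 412 = 1648. This matches "The total sample size calculated is 1648 with 412 in each group".

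**2. What each listed analysis does with a participant who lacks only month 6** (reading the rule as filling month 12 only):

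| Analysis | Stated for | Participant kept? |
|---|---|---|
| Mixed model, time by group | SBP | yes, through the observed visits |
| Repeated-measures ANOVA | SBP, adherence | no |
| Friedman (within group) | SBP, adherence | no |
| ANOVA, Kruskal-Wallis at month 6 | SBP, adherence | no |
| Chi-square at month 6 | pill-count adherence | no |
| ANOVA, Kruskal-Wallis at month 12 | SBP, adherence | yes |

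**3. Check by simulation.** One data set was generated with 4 × 412 participants, SD 18.5 and an assumed between-visit correlation of 0.5. Month-6 values were removed at random with an assumed probability of 15%, and month 12 was left complete. The mixed model used all 1648 participants. An analysis needing all three visits kept 1416, a loss of 232 (232 / 1648 = 14%).

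**4. Does planned power suffer?** The protocol gives no month-6 missingness, so a range is assumed. With month 12 imputed, the number left per group is 412 × (1 − p). Power for 5 mmHg is Φ(5 / (18.5 × √(2/n)) − 1.960):

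| Missing month 6 (assumed) | Left per group | Power |
|---|---|---|
| 5% | 391 | 0.966 |
| 10% | 371 | 0.957 |
| 15% | 350 | 0.947 |
| 20% | 330 | 0.934 |
| 30% | 288 | 0.901 |

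These count an imputed month-12 value as fully informative, so they are upper limits. On this count, power does not fall below the planned 90% even at 30%.

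**5. Can the bias be sized?** Only by assumption. Suppose about 16% to 19% miss month 6 in one arm, more often with high baseline SBP (log-odds slope 0.5 or 1.0 per SD, correlation 0.5). The raw month-6 mean among attenders in that arm then shifts by about −0.7 or −1.5 to −1.6 mmHg. Under the same mechanism the complete-case change from baseline shifts the other way, by about +0.7 or +1.5. After conditioning on baseline, the bias is 0.00 to −0.01. Size and sign therefore depend on the estimand and on inputs that the document does not give.

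**The case against.** The strongest reply is that the mixed model is named first, specifically for the primary outcome, and estimates a treatment effect at each visit. It keeps participants who miss month 6 and is valid under missing-at-random. That stands. A reader might infer that the month-6 SBP comparison as a whole is complete-case, or that observed 12-month SBP is lost to the trial. Neither follows, because the mixed model and the single-visit tests at month 12 both use those values. Friedman and Wilcoxon signed-rank are moreover within-group tests and do not carry the randomised comparison.

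Second, the closing words of the imputation sentence may say when imputation is done (at the final analysis) rather than which visit it fills. The text does not settle this, so a reader should not take it as fact that month-6 values stay missing. The ambiguity remains a fault of wording. It would also be wrong to argue that Tukey comparisons cannot be pooled after imputation: they are mean differences with standard errors.

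Third, a reader might infer that power falls. Starting from the 288 per group expected at month 12, losing 5% to 15% would give about 0.89 to 0.85. That base assumes month 12 is not imputed, which contradicts the stated rule. Nor do the shifts in step 5 measure the planned contrast, since they describe one arm under invented missingness that the mixed model would handle.

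Fourth, a fuller analysis plan is announced and may settle imputation detail. That is fair for the choice of imputation variables. It does not cover tests that the protocol already commits to, for two outcomes, beside a better method and without ranking.

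**Conclusion.** The concern holds in limited form. The protocol commits to complete-data tests for SBP and adherence, gives them no rank below the mixed model, omits that model from the abstract, and has one missing-data rule tied to 12 months. If the rule fills month 12 only, repeated-measures ANOVA and Friedman exclude participants without month 6, and the month-6 single-visit comparisons rest on attenders. This conflicts with the declared intention-to-treat analysis and matters most for adherence.

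The number excluded follows whatever share misses month 6: 232 of 1648 in the simulated data set with an assumed 15%. Bias arises only if month-6 missingness differs by arm in a way related to outcome, and its size cannot be derived from the document. The mixed-model SBP comparison is not affected, and no loss of planned power is shown. The text should be changed, but the point does not threaten the final SBP result if the mixed model is what is reported.

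**What to change.** - State that SBP at 0, 6 and 12 months is analysed with the mixed model, using every observed visit of all randomised participants, and that this analysis takes precedence. Bring the abstract into line.
- Use the same model for SEAMS scores.
- Remove repeated-measures ANOVA and Friedman, or label them descriptive.
- Where multiple imputation is kept, for example for the binary pill-count and SBP-control outcomes, impute months 6 and 12 jointly by arm, and reword the sentence so that it names the visits covered.

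Cost: protocol and analysis-plan wording and slightly different code. No new data, visits or participants are needed.
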